### Outcome measures

The hypothesised benefits of a CBA are;

a) improvements in pain and LBP disability,

b) improved tolerance to pain, increased self-efficacy and decreased depression,

c) improvements in overall quality of life

d) an increase in activity, particularly in those activities that are avoided due to fear of pain or symptoms,

e) a shift toward self-management of LBP symptoms and disability,

f) a reduction in use of self-paid and/or NHS treatments.

The outcome measures (shown in Table 1) have been selected to cover these domains, and to maximise generalisability, and have utilised the outcome data set recommended by the International Low Back Pain Forum where appropriate [2]. The primary outcome is the Roland and Morris Questionnaire which (RMDQ) [31] is one of the most widely used measures for LBP in primary care. It has acceptable reliability [32,2,33] but concerns are emerging about its scalability and sensitivity to clinically important change [34]. Therefore, have a second primary outcome with the modified Von Korff Scale [35] and we will undertake additional analyses to compare the psychometric properties of the two measures. The secondary outcome measures are:

(i) the number of days (defined as greater than 1/2 a day) participants have had to cut down on normal activity in the preceding four weeks;

(ii) number of days participants had time off work because of low back pain or leg pain (sciatica);

(iii) psychological measures as captured on the fear avoidance beliefs questionnaire, pain self-efficacy

(iv) health-related quality of life as assessed using the SF-12 Version 2;

(v) satisfaction with treatment measured using a standardised and recommended single-item question [2] – 'How satisfied are you with the treatment you received?'. The response is measured on a five point Likert scale ranging from very dissatisfied to very satisfied.

If the intervention is successful participants should be able to utilise cognitive skills to manage symptoms over a prolonged period; so we will measure the potential benefits over a 12-month follow up period. The timing of various assessments is shown in Table 1.

### Sample size

The sample size has been estimated using well-documented methods [36], with careful consideration of the practicalities to ensure that sufficient numbers of participants are randomised within an acceptable time frame. We originally planned a 1:1 randomisation ratio between CBA and usual care. Early in the trial we recognised that a 2:1 randomisation (in favour of CBA) had distinct advantages in ensuring that sufficient numbers of patients are randomised to sustain the group sessions. A randomisation balance of 2:1 can be adopted with inconsequential loss of power, but further imbalances necessitate an increase in study size. From a list size of 100,000 (approximating to one location), with twice as many participants being randomised to the intervention group, we estimated the yield of participants randomised to the group sessions was 1.4 per week, allowing us to recruit eight participants to a new group starting every six weeks. This estimate was based on data from the UK BEAM trial [37].

The potential impact of the group effect was also considered in the sample size estimation. In this trial, other effects include the individual practitioner treating several groups, regions and organisations. We perceive that the most potent of the cluster effects is the group effect, and is the only effect to have been considered formally in the sample size estimation (using methods described by [38]).

The sample size target for the trial is 700 to detect a moderate effect size, and a difference between the groups of approximately 1.8 RDQ points, assuming a standard deviation of 4.27 points (giving an effect size of 0.42). Approximately 233 participants will be randomised to active management alone and 467 participants on the active management + CBA arm of the trial. The sample size has been inflated to account for an inter-cluster correlation co-efficient of 0.01 (based on UK – BEAM [37] and incorporates a loss to follow up of 25%. We have used a power of 90% and p < 0.01 [39]. Effect sizes of approximately 0.4 are considered to be clinically worthwhile for back pain interventions [23]. The sample size requirement will be reviewed by an independent data monitoring committee at approximately the mid point of data accumulation.

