### Data analysis

Primary analyses will be by intention-to-treat, i.e. patients will be analysed in the groups to which they were randomised, regardless of the treatment that they may have received. The main study outcomes will be summarised as the Area under the Curve (AUC) over the 12 month follow up period. The AUC will be calculated by summing areas under the graph between each pair of consecutive observations for an individual. Thus the AUC is a weighted average of the outcome scores at each individual time point weighted by the time between the observations. Mean/median (depending on the distribution of the data) AUC between the two treatment groups will then be compared by a two independent sample t-test/Wilcoxon rank sum test and include reporting of the 95% confidence intervals for the mean/median difference in the AUCs. One of the advantages of the AUC method is that a sensitivity analysis may be easily performed to investigate the effect of missing data. In the case of large missing data, imputation techniques will be considered. In addition outcomes will be reported separately for the 3 month time point to characterise the early response to treatment. Multi-level modelling will be used to estimate group, therapist and other effects as appropriate.

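### The allocation ratio appears to have changed from 1:1 to 2:1 after the trial began, but the main AUC comparison is pooled and unadjusted, so outcome drift between the two periods can bias it

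*Protocol article*

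**What the plan says.** The Sample size section of the protocol article gives the history of the ratio: "We originally planned a 1:1 randomisation ratio between CBA and usual care", followed by "Early in the trial we recognised that a 2:1 randomisation (in favour of CBA) had distinct advantages". The reason given is to keep the treatment groups filled. The planned arm sizes follow: "Approximately 233 participants will be randomised to active management alone and 467 participants" to active management plus CBA. The section does not say when the ratio changed, whether all centres changed together, or how many people had been randomised by then.

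The Treatment allocation section describes minimisation by a central office, using centre and level of troublesomeness. It does not say how the algorithm handled a change of ratio.

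The Data analysis section summarises each main outcome as an AUC over 12 months, described as a time-weighted average of the scores. The arms "will then be compared by a two independent sample t-test/Wilcoxon rank sum test". No covariate is named for that comparison. A separate sentence foresees multi-level models to estimate group, therapist and other effects where appropriate; allocation period is not named there.

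**The concern.** A participant randomised at 1:1 has a 1/2 chance of CBA; one randomised at 2:1 has a 2/3 chance. Within each period randomisation makes the arms comparable. Once the periods are pooled without adjustment, the arms differ systematically in their mix of early and late recruits, with proportionally more early recruits among controls. If early and late recruits differ in mean outcome for any reason, part of that difference enters the treatment estimate. If early recruits score worse, CBA is flattered; if they score better, CBA is penalised. Minimisation on centre and troublesomeness does not balance calendar period, and the named test does not correct for it.

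**Working it through.** **Inputs from the article (Sample size section).** Total 700; target difference 1.8 RMDQ points; SD 4.27; loss to follow-up 25%; ratios 1:1 and then 2:1. The total of 700 is taken as given, because the point turns only on the split.

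**Inputs the article does not give (assumptions).** f, the share of participants randomised at 1:1, taken as 5% to 20%. S, the difference in mean outcome between early and late recruits on the RMDQ scale, shown per 1 point and at 2 points. The treatment effect is taken as the same in both periods.

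**The plan's own split.** 700 × 1/3 = 233 and 700 × 2/3 = 467. The stated arm sizes therefore reproduce as 2:1 over all 700, leaving no room for a 1:1 period.

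**Arm sizes with a 1:1 period.** Controls = 700 × [f/2 + (1−f)/3] = 700 × (2+f)/6. CBA = 700 × (4−f)/6.

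**Share of early recruits in each arm.** Controls: (f/2) ÷ [(2+f)/6] = 3f/(2+f). CBA: 3f/(4−f).

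**Imbalance and bias.** D = 3f/(2+f) − 3f/(4−f). The bias in the crude difference is D × S.

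| f | Controls / CBA | Early share, controls v CBA | D (bias per 1 point) | Bias if S = 2 | As % of 1.8 |
|---|---|---|---|---|---|
| 5% | 239 / 461 | 7.3% v 3.8% | 0.035 | 0.07 | 3.9% |
| 10% | 245 / 455 | 14.3% v 7.7% | 0.066 | 0.13 | 7.3% |
| 20% | 257 / 443 | 27.3% v 15.8% | 0.115 | 0.23 | 12.8% |

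**Effect on the error rate.** With 700 × 0.75 = 525 followed up, SE = 4.27 × √(1/n_control + 1/n_CBA), which is 0.393 at f = 5% and 0.387 at f = 20%, ignoring clustering. A nominal two-sided 5% test then has a true error rate of 5.1% (f = 5%) to 6.0% (f = 20%) if S = 1, and 5.4% to 9.1% if S = 2.

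**What the stated split allows.** Suppose the control arm lies within 3% of 233, that is, up to 240. Then (2+f)/6 × 700 ≤ 240 gives f ≤ about 6%. D is then about 0.04, so S of 2 to 3 points gives 0.08 to 0.12 RMDQ points, or 4% to 7% of 1.8.

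**When that bound fails.** If later allocation was tilted so that the whole trial ends at 2:1, the final split is 1/3 to 2/3 whatever f is. The imbalance becomes (f/2)/(1/3) − (f/2)/(2/3) = 0.75f, which is 0.0375 at f = 5% and 0.15 at f = 20%. The split then says nothing about f, and the imbalance is somewhat larger than in the table.

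**Cost of adjusting for period.** The variance ratio, adjusted to pooled, is [(2+f)/6 × (4−f)/6] ÷ [f/4 + 2(1−f)/9]. At f = 5% this is 0.2249/0.2236 = 1.006; at f = 20% it is 0.2322/0.2278 = 1.02. The loss is 0.6% to 2%.

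**The case against.** The article never says that anyone was randomised at 1:1, and the only arm sizes it gives are 2:1 over the whole trial. If the change came before the first randomisation, the bias is zero; if soon after, it is small. A 2-point drift is also severe: 2/4.27 = 0.47 SD, more than the 0.42 the trial is powered to detect. There is one set of eligibility criteria, and nothing in the article shows that case-mix changed over time. Covariate lists are commonly left to an analysis plan, which is not shown, and multi-level modelling is mentioned.

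Most of this stands as a limit on size. It does not remove the point. The phrase about the trial's early stage most naturally means that randomisation had begun, and the article does not leave the main comparison open: it names an unadjusted test. The multi-level models are offered to estimate other effects, not as a replacement for that test.

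A reader might infer more than the article supports:

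- **That the result is confounded.** Neither the number at 1:1 nor any drift is stated, so only a possibility is shown.
- **That the bias persists however large the trial.** A 1:1 period at the start is a fixed block whose weight falls as recruitment goes on. With 100 people at 1:1, D is 0.089 at a total of 700 and 0.049 at 1,400.
- **That controls come disproportionately from the centres that opened first.** Minimisation on centre may limit this, and how it handled the change is not stated.
- **That the near-equal numbers in the Treatment allocation section contradict 2:1.** That sentence concerns the spread across centres within each arm, not equality between arms, and is compatible with 2:1.

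**Conclusion.** The point holds as a conditional weakness in the choice of primary analysis. It rests on two things the article does not state: that some participants were randomised at 1:1, and that mean outcome differed between the periods. Given both, the crude AUC difference is biased by about 0.035 to 0.115 RMDQ points per 1-point difference between periods, for 5% to 20% randomised at 1:1. The 233/467 split favours the low end, where even a 2-point drift costs about 4% of the target difference. That reassurance lapses if later allocation was tilted to bring the whole trial back to 2:1. The likely effect is small, but the analysis as worded gives no protection against it and the remedy costs almost nothing.

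**What to change.** Replace the two-sample test as the primary comparison with a regression model on AUC, with treatment, allocation period (before or after the ratio change), centre and troublesomeness as covariates. State the date of the change and the number randomised at 1:1, and base the expected arm sizes on that number; if it is zero, say so, and the period term falls away. A sensitivity analysis restricted to participants randomised at 2:1 is optional.

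The cost is a wording change and a few degrees of freedom: one for period, one for troublesomeness, and one fewer than the number of centres. The period term adds 0.6% to 2% to the variance over the range shown. Period can be derived from randomisation dates, which the central office should hold. The article says recruitment was still open, so the change could be made before outcomes are analysed.

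### The trial is sized at p < 0.01 for the RDQ, but the analysis section gives only 95% intervals for two primary outcomes and does not carry the 1% level forward

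*Protocol article*

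**What the plan says.** - **Protocol article, Sample size.** The level and power are given in one sentence: "We have used a power of 90% and p < 0.01 [39". Sidedness is not stated. The target effect concerns one instrument only: "a difference between the groups of approximately 1.8 RDQ points, assuming a standard deviation of 4.27 points (giving an effect size of 0.42". The total is 700, split about 233 to 467, with 25% loss to follow-up and an intracluster correlation of 0.01.
- **Protocol article, Data analysis.** Each main outcome is summarised as an area under the curve over 12 months and compared between arms by a two-sample t-test or a Wilcoxon rank sum test. The plan is also to "include reporting of the 95% confidence intervals for the mean/median difference in the AUCs". That 95% is the only inferential level in the section.
- **Protocol article, Outcome measures and Table 1.** The text says "The primary outcome is the Roland and Morris Questionnaire which (RMDQ) [31" and then, citing concerns about how well that instrument scales and detects change, that the investigators "have a second primary outcome with the modified Von Korff Scale [35". Table 1 lists both as primary, and the abstract also uses the plural.

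The article writes RDQ in the sample size section and RMDQ elsewhere. I take these to be the same instrument.

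**The concern.** A trial sized at 1% implies that 1% is the standard of evidence its designers wanted. The section that a reader will use to interpret the results offers 95% intervals and nothing else, for two outcomes that are both called primary. Someone reading the results from this article could reasonably treat a 95% interval that excludes zero, on either outcome, as a positive trial. That is a looser standard than the one used for sizing, and it is applied twice.

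Disagreement between the two outcomes is a realistic prospect. The second was added because the investigators doubted the first instrument's scaling and sensitivity to change. If the level is settled only once results are known, the choice can follow the favourable outcome.

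**Working it through.** **Inputs.** From Sample size: difference d = 1.8, SD s = 4.27, power 90%, level 0.01, allocation 2:1 (467:233), loss 25%, intracluster correlation 0.01. From Experimental intervention: group size m of 6 to 8. Assumed: two-sided testing, the correlation between the two test statistics, and 4.27 as the SD of the RDQ summary that is tested.

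**Step 1: the plan's own sample size.** With k = 2,

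n(control) = (1 + 1/k) × [s × (2.576 + 1.282) / d]² = 1.5 × [4.27 × 3.858 / 1.8]² ≈ 126.

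The total analysed is 126 × 3 = 378. Allowing for 25% loss gives 378 / 0.75 = 504. The design effect 1 + (m − 1) × 0.01 is 1.05 to 1.07, which gives 529 to 539. The stated 700 is not reproduced, but it exceeds what these inputs require, so power is not short.

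**Step 2: RDQ power with 700 randomised.** After 25% loss, 174.75 and 350.25 remain.

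- Standard error = 4.27 × √(1/174.75 + 1/350.25) = 0.395, and 1.8 / 0.395 = 4.55.
- Dividing by √1.07 or √1.05 for clustering gives 4.40 or 4.44.
- At two-sided 0.01: 4.40 − 2.576 = 1.82 and 4.44 − 2.576 = 1.87, so power is 96.6% to 96.9%.
- At two-sided 0.005: 4.40 − 2.807 = 1.59 and 4.44 − 2.807 = 1.63, so power is 94.4% to 94.9%.

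**Step 3: chance of at least one false positive across two outcomes.** For independent tests at level a it is 1 − (1 − a)²: 1 − 0.95² = 0.0975 and 1 − 0.99² = 0.0199. For correlated tests it is 1 − P(both |Z| below the cut-off) under a bivariate normal distribution.

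| Correlation (assumed) | Either outcome at 0.05 | Either outcome at 0.01 |
|---|---|---|
| 0 | 0.0975 | 0.0199 |
| 0.3 | 0.0951 | 0.0196 |
| 0.5 | 0.0907 | 0.0190 |
| 0.7 | 0.0835 | 0.0177 |
| 0.8 | 0.0781 | 0.0166 |
| 0.9 | 0.0704 | 0.0149 |

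The middle column is 7 to 10 times 0.01. The right-hand column is at most twice 0.01. At 0.005 per outcome the total cannot exceed 2 × 0.005 = 0.01.

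**Step 4: what the choice of level changes for the RDQ.** With a design effect of 1.07 the standard error is 0.395 × √1.07 = 0.409. An observed difference has to exceed 1.960 × 0.409 = 0.80 points for the 95% interval to exclude zero, and 2.576 × 0.409 = 1.05 points for the 99% interval. Differences between about 0.80 and 1.05 points are where the two readings part.

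**The case against.** A reader might infer that the trial's false-positive rate is in fact several times the planned one. The article does not support that, for four reasons.

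- The data analysis section specifies a hypothesis test and adds the interval as reporting. Nowhere does it say that benefit is declared when a 95% interval excludes zero. A 95% interval can properly stand beside a test at 0.01, and 0.01 is the only significance level in the article.
- The article does not say that success on either outcome is enough. If both had to succeed at 0.05, the error rate would be at most 5%.
- The 0.01 may itself have been chosen to allow for two outcomes. The article does not say so.
- The article condenses a fuller protocol, and an analysis plan may exist. A rule for combining the outcomes may be there, so its absence here is not a fault in itself.

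These objections are sound and they make the inflation conditional. They do not remove the mismatch in what is written: one level in the sizing, another as the only level in the analysis, and two primary outcomes where one is first called the primary. If 0.01 was meant as the test level or as the allowance for two outcomes, the analysis section is where it should be carried through.

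It is also tempting to count the Von Korff scale as two scores and hence three tests. Table 1 has a single primary entry for it, so that reading has no basis in the document.

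**Conclusion.** The point holds as an unreconciled statement of error levels, not as a demonstrated inflation. If either primary outcome were judged by its 95% interval, the family-wise error would be 7.0% to 9.75%, against 1% in the sizing. If each is tested at two-sided 0.01, it is at most 2%. The range rests on assumed correlations of 0.9 to 0, on two-sided testing, and on an either-outcome rule that the article does not state.

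This is a wording correction worth making before the data are analysed by arm. It is not a defect that undermines the design. That the planned 700 is enough at the stricter level is shown for the RDQ only. The article gives no difference or SD for the Von Korff scale.

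**What to change.** In the data analysis section:

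1. State that each of the two primary outcomes is tested at the sizing level of 0.01, and state the sidedness (two-sided is assumed here). If 1% was meant to cover both outcomes together, state 0.005 for each instead.
2. State that benefit is claimed on an outcome only when its own test meets that level.
3. Give intervals that match the test, 99% (or 99.5%), for the two primary outcomes, and keep the 95% intervals as description.

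**Cost.** The 99% intervals are about 31% wider than the 95% ones (2.576 / 1.960 = 1.31), and 99.5% intervals about 43% wider (2.807 / 1.960 = 1.43). The RDQ needs no extra participants: power is about 97% at 0.01 and 94% to 95% at 0.005. Testing each outcome at 0.01 accepts up to 2% overall, while 0.005 each holds 1% for a small loss of power. Power for the Von Korff scale at either level stays unknown until a target difference and SD are supplied.

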### Data analysis

Primary analyses will be by intention-to-treat, i.e. patients will be analysed in the groups to which they were randomised, regardless of the treatment that they may have received. The main study outcomes will be summarised as the Area under the Curve (AUC) over the 12 month follow up period. The AUC will be calculated by summing areas under the graph between each pair of consecutive observations for an individual. Thus the AUC is a weighted average of the outcome scores at each individual time point weighted by the time between the observations. Mean/median (depending on the distribution of the data) AUC between the two treatment groups will then be compared by a two independent sample t-test/Wilcoxon rank sum test and include reporting of the 95% confidence intervals for the mean/median difference in the AUCs. One of the advantages of the AUC method is that a sensitivity analysis may be easily performed to investigate the effect of missing data. In the case of large missing data, imputation techniques will be considered. In addition outcomes will be reported separately for the 3 month time point to characterise the early response to treatment. Multi-level modelling will be used to estimate group, therapist and other effects as appropriate.

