### Baseline Assessment

Data are collected using a standard pro forma administered by a specially trained research nurse. These include age, gender, ethnicity, educational attainment, general health status, duration of LBP, symptoms, recent treatment history, anxiety and depression (using the Hospital Anxiety and Depression Scale [29]) and employment status. In addition participants complete the baseline (pre-intervention) versions of the outcome measure package (see Table 1).

**Table 1 T1:** Outcomes measures

	Domain	Measures	Time points (months)
Primary	Pain & Disability	Roland & Morris Questionnaire (Roland 1983)	0, 3, 6, 12
	Pain	Von Korff Scale (Von Korff 1992)	0, 3, 6, 12
Secondary	Occupational and other limitations	Numbers of days off work, reduced activity and bed rest	0, 3, 6, 12
	Health related quality of life inc physical & mental health	Short Form 12 version 2 (Ware 1996)	0, 3, 6, 12
	Back Pain Beliefs	Fear avoidance scale (1^st ^five items only)* (Waddell 1993)	0, 3, 6, 12
	Self-efficacy	Pain self-efficacy questionnaire (Nicholas 2006)	0, 3, 6, 12
	Satisfaction with treatment	Single item rating of satisfaction with treatment (Deyo et al 1998)	12
Economic analysis	Resource Use	Resource use questionnaire	6, 12
	Health related quality of life; time trade off score	EQ-5D (health utility) (EuroQol Group 1990)	0, 6, 12

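### The 12-month AUC is compared unadjusted, gives the pre-treatment score one eighth of the weight, has no stated divisor when the last visit is missing, and is backed by separate reporting at month 3 only

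*Protocol article*

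**What the plan says.** All references are to the protocol article.

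- **Summary measure (Data analysis).** "The main study outcomes will be summarised as the Area under the Curve (AUC) over the 12 month follow up period".
- **Construction (Data analysis).** "The AUC will be calculated by summing areas under the graph between each pair of consecutive observations for an individual". The next sentence reads "Thus the AUC is a weighted average of the outcome scores at each individual time point weighted by the time between the observations". No divisor is given, and nothing is said about a person whose last visit is missing.
- **Comparison (Data analysis).** The AUCs are compared by a two-sample t-test or a rank-sum test. No baseline covariate is named. Multi-level modelling is foreseen for group, therapist and other effects.
- **Visits (Table 1).** Both primary outcomes are measured at months 0, 3, 6 and 12. The Baseline Assessment section describes the month-0 set as pre-intervention.
- **Missing data.** The sample size "incorporates a loss to follow up of 25" per cent. A sensitivity analysis is described as easy to do, and "In the case of large missing data, imputation techniques will be considered".
- **Separate time points (Data analysis).** "In addition outcomes will be reported separately for the 3 month time point to characterise the early response to treatment".
- **Aim (Outcome measures).** The 12-month follow-up is justified because, if treatment works, "participants should be able to utilise cognitive skills to manage symptoms over a prolonged period".

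**The concern.** There are three linked weaknesses in the method as stated.

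1. A trapezoid over 0 to 12 months needs the month-0 score, where no treatment effect can exist. The unadjusted test then leaves between-person baseline variation in the comparison, although the score that would remove it is collected on everyone.
2. A sum of areas and a weighted average are different quantities once a person's follow-up is cut short. The sentences do not say which applies, or over what time base. With a quarter of participants expected to be lost, the primary estimate depends on a choice that could be made after the data are seen.
3. A single average over 12 months cannot separate an effect that lasts from one that has faded. Month 3 is the only time point promised separately, yet durability is the reason given for following people to 12 months.

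**Working it through.** **Inputs.** From the protocol: visits at 0, 3, 6 and 12 months (Table 1); target difference 1.8 points, SD 4.27 and 25% loss (Sample size). Assumed for illustration, because the protocol gives no such figures: a flat score of 9, loss by arm, and a common between-visit correlation r with equal variances.

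**The plan's own figure.** 1.8 / 4.27 = 0.42, which reproduces the stated effect size. It is the standardised difference of a single score, not of an AUC. The AUC rule has no stated figure to reproduce.

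**Weights with complete data.** Each visit receives half of each adjoining interval: 1.5, 3, 4.5 and 3 months. Divided by 12, these are 0.125, 0.25, 0.375 and 0.25. A constant 1.8-point effect at months 3, 6 and 12 becomes 1.8 × (0.25 + 0.375 + 0.25) = 1.8 × 0.875 = 1.575.

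**Cost of leaving baseline unadjusted.** For weights w, the variance is 4.27² × [Σw² + r(1 − Σw²)]. Adjusting for baseline removes the square of the covariance with month 0. For the three follow-up visits alone, rescaling by 0.875 gives weights 2/7, 3/7 and 2/7. Σw² is 0.28125 for the AUC and 17/49 = 0.347 for the follow-up average.

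| r | 0–12 AUC, unadjusted: effect / SD | Follow-up average, unadjusted | Follow-up average, baseline-adjusted |
|---|---|---|---|
| 0.5 | 1.575 / 3.418 = 0.46 | 1.8 / 3.504 = 0.51 | 1.8 / 2.779 = 0.65 |
| 0.6 | 1.575 / 3.604 = 0.44 | 1.8 / 3.670 = 0.49 | 1.8 / 2.628 = 0.68 |
| 0.7 | 1.575 / 3.782 = 0.42 | 1.8 / 3.829 = 0.47 | 1.8 / 2.393 = 0.75 |
| 0.8 | 1.575 / 3.951 = 0.40 | 1.8 / 3.981 = 0.45 | 1.8 / 2.045 = 0.88 |

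Most of the gain comes from adjustment. Once baseline is a covariate, the AUC and the follow-up average differ only by the factor 0.875.

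**Missing last visit, sum reading (flat score 9).** Seen to month 12: 9 × 12 = 108 score-months. Last seen at month 6: 9 × 6 = 54. Last seen at month 3: 9 × 3 = 27. With no true effect, the spurious mean difference is (difference in proportion lost after month 6) × 54, divided by 12 to return to points:

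- equal loss: 0;
- 30% v 25%: 0.05 × 54 = 2.7, or 0.225 points;
- 30% v 20%: 0.10 × 54 = 5.4, or 0.45 points, a quarter of 1.8.

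The arm with more loss appears better, since higher scores are worse.

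**Missing last visit, average over observed time.** The flat person scores 9.0 in all three patterns, so the shrinkage disappears. The weights become 0.25, 0.5 and 0.25 if last seen at month 6, or 0.5 and 0.5 if last seen at month 3. The baseline weight therefore goes from 0.125 to 0.25 or 0.50. A person improving 9, 8, 7, 6 scores:

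- complete: (13.5 + 24 + 31.5 + 18) / 12 = 7.25;
- to month 6: (13.5 + 24 + 10.5) / 6 = 8.0;
- to month 3: (13.5 + 12) / 3 = 8.5.

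Truncation now makes an improver look worse. A missed middle visit with month 12 present keeps the full 12-month span under either reading.

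**Fading effect.** Effects of 3.0, 1.8 and 0 points at months 3, 6 and 12 give 0.75 + 0.675 + 0 = 1.425 in the AUC. A constant effect of 1.425 / 0.875 = 1.63 gives the same. Effects of 2.4, 2.4 and 0 give 0.6 + 0.9 = 1.50, close to the 1.575 of a fully sustained 1.8.

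**The case against.** **Dropouts look better, so the trial is biased.** A reader might infer this from the summing sentence alone. The documents do not support it: the next sentence calls the AUC a weighted average, under which a flat score is unchanged by truncation and an improver looks worse. Nor do they predict unequal loss. The 25% is an overall figure, Table 1 gives one schedule for the whole trial, and nothing ties outcome collection to attending groups. Equal loss gives zero mean bias even under the sum.

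**Counting baseline biases the comparison or leaves the trial underpowered.** Neither follows. Randomisation makes baseline equal in expectation. Averaging visits also lowers the SD, so the unadjusted AUC has a standardised effect of 0.40 to 0.46 over the correlations above, against the planned 0.42. What stands is an effect on a diluted scale and precision given away.

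**The analysis will be restricted to completers, against intention to treat.** The plan states no such rule, so this cannot be charged to it.

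**The long-term question will go unanswered.** This is too strong. Month-12 scores are collected, and naming month 3 does not forbid reporting month 12. A time average is also a legitimate target for benefit over a year. What stands is that the only separate estimate committed to is the early one.

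**This is detail for the full analysis plan.** Imputation methods and thresholds may indeed sit there, and their absence from an article is not criticised. The AUC definition and the unadjusted test, however, are stated here, and the two definition sentences do not agree.

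**Conclusion.** The point holds as a defect of method and definition, not as a demonstrated bias. Three statements can be made.

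- With complete data and month 0 included, which is the natural reading though not stated outright, a sustained 1.8-point effect is reported as 1.575, a dilution of 12.5%, and baseline variation is left in the test.
- With a missing last visit, the estimate depends on an unstated divisor, and the error can run in either direction. Under the sum reading its size is 0 to 0.45 points over the assumed loss patterns shown (flat score 9; equal, 30% v 25%, 30% v 20%). These inputs are illustrative and do not come from the protocol.
- The stated reporting does not commit to showing whether benefit lasts to month 12, and the AUC cannot show it.

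The precision figures rest on equal variances and a common correlation of 0.5 to 0.8 between visits.

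**What to change.** **Preferred.** Analyse the 3-, 6- and 12-month scores in a linear mixed model with arm, time, arm-by-time and the baseline score as covariate, keeping the planned multi-level terms for therapy group. Take as primary contrast the time-weighted mean of the three arm differences with weights 2/7, 3/7 and 2/7. These are the AUC's own follow-up weights without month 0. Everyone with at least one follow-up score contributes.

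**Minimum.** Keep a summary measure, but make it a follow-up average over a fixed time base, adjust it for baseline, and state in advance what is done when the last visit is missing.

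**In either case.** Name the 12-month difference for separate reporting alongside month 3. This is needed because the averaged contrast is as blind to fading as the AUC: effects of 3.0, 1.8 and 0 give (6 + 5.4 + 0) / 7 = 1.63, the same as a constant 1.63.

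**Cost.** Changes to the analysis wording and slightly more analysis work; no new data. The mixed model relies on data being missing at random, which should be stated, and it leaves out people with no follow-up score. Multiple imputation should be specified as the sensitivity analysis.
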